## Abstract

**Background:**

Substance use is a high-impact biopsychosocial problem in Chile, where 21% of adults have experienced a severe alcohol use episode. In the past year, the prevalence rates were 12.5% for marijuana, 0.8% for cocaine, and 0.4% for cocaine base paste. Cannabis prevalence in Chile is higher than the global (4.2%) and South American (3.58%) averages. Cocaine prevalence in Chile is lower than in South America (1.62%) but higher than the global average (0.42%). No international reports are available for cocaine base paste. Mental health and substance use programs in Chilean primary care involve psychologists and social workers. Solution-focused brief interventions (SFBIs) are based on solution-focused brief therapy, a strengths-based and person-centered approach in which practitioners adopt a stance of “not being the expert,” respecting clients’ needs and perspectives.

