## Introduction

### Overview

Substance use is a high-impact biopsychosocial problem in Chile. Chile has one of the highest levels of alcohol consumption per capita on the continent, with rates of 15% for men and 3.7% for women [1]. In addition, 21% of the population have experienced a severe alcohol episode, compared with the global average of 18% [1]. These high levels of alcohol consumption are associated with health indicators, including cirrhosis prevalence and alcohol-related causes of death [2]. Furthermore, illicit drug use in Chile showed a prevalence of 12.5% in the past year and 12.7% in the past month for marijuana (18.1% for men and 7.4% for women), 0.76% in the past year and 1% in the past month for cocaine (1.8% for men and 0.3% for women), and 0.4% in the past month for cocaine base paste (0.7% for men and 0.2% for women) [3,4]. The rates of cannabis use in Chile are concerning when compared with the global and South American prevalence. The global prevalence of marijuana is 4.12%, and in South America it is 3.58%. Cocaine prevalence is lower in Chile than in the rest of South America (1.62%) but remains higher than the global prevalence (0.42%) [5]. No international reports are available for cocaine base paste. In terms of age groups, marijuana and cocaine use is more common among individuals aged 19-25 years, whereas cocaine base paste is more prevalent among individuals aged 26-34 years [3]. Drug-related deaths have tripled in the Americas and are among the top 10 causes of disability-adjusted life years [6].

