### Hypotheses

This study has the following hypotheses. First, participants who receive the SFBI will decrease their substance use patterns and risk-level use of alcohol, marijuana, cocaine, and cocaine base paste. Second, participants receiving the SFBI will report positive changes in the consequences associated with alcohol, marijuana, cocaine, and cocaine base paste use, as well as improvements in mental health symptoms between baseline and follow-ups. Third, when comparing outcomes between the intervention group and the usual care group, it is expected that participants in the intervention group will show greater reductions in substance use, consequences of use, and mental health symptoms than those receiving usual care. Finally, both participants and professionals involved in the intervention group will report experiences indicating that the model is acceptable and relevant for implementation in primary care.

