### Sample Size

The necessary sample size was calculated considering the minimum effect size found in evidence-based psychosocial interventions for substance use disorders (Cohen *d*=0.24 for polysubstance use, equivalent to Cohen *f*=0.12) [35]. The calculation was performed using the G*Power (Heinrich-Heine-Universität Düsseldorf) statistical software for sample size calculation [36], considering 80% power and a significance level of 5%. For the interaction effect between within-subject and between-subject factors in mixed ANOVA (details available in the Analysis Plan section), a sample size of 96 individuals was obtained, and after considering a 40% attrition rate [24,35] in follow-up, it increases to 160 individuals. The evaluation of the SFBI will be conducted separately by substance type (evaluating its effectiveness separately for at least alcohol, cocaine, and cocaine base paste, considering possible overlaps between them and marijuana). Thus, we plan to recruit 320 participants.

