### Recruitment

Since in PHC centers the Alcohol, Smoking, and Substance Involvement Screening Test (ASSIST) is applied routinely—in preventive check-ups—to individuals aged 20-65 years, the staff members responsible for applying this test at each PHC clinic will invite individuals whose scores are equal to or higher than 11 on the ASSIST for alcohol and 4 for other substances to participate in this study. If they accept, they will be given an appointment with the research coordinator or a research assistant, who will formally invite them to participate.

The inclusion criteria are as follows: participants must have an ASSIST score of 11 or higher for alcohol and a score of 4 or higher for other substances, be able to communicate verbally with others, be willing to participate in the intervention, and be willing to complete the measurement instruments.

The exclusion criteria are as follows: participants with a severe and untreated mental illness such as schizophrenia, those not willing to participate in the intervention, those not willing to complete the measurement instruments, those who have received another brief intervention within the last year, and those currently being treated in another program for substance use will not be eligible to participate.

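### Marijuana is one of four substances in the hypotheses, but the plan commits to separate evaluations of only the other three, and 320 participants cover just two non-overlapping evaluations

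*Protocol article*

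**What the plan says.** **Hypotheses.** The first hypothesis is that SFBI participants "will decrease their substance use patterns and risk-level use of alcohol, marijuana, cocaine, and cocaine base paste". The second expects "positive changes in the consequences associated with alcohol, marijuana, cocaine, and cocaine base paste use". Both name the same four substances. The third compares the arms on substance use without naming any.

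**Sample Size.** The section says that the SFBI will be evaluated separately by substance type and then specifies "evaluating its effectiveness separately for at least alcohol, cocaine, and cocaine base paste, considering possible overlaps between them and marijuana". It derives 96 participants for the group-by-time interaction in a mixed ANOVA, raises this to 160 for 40% attrition, and sets recruitment at 320.

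**Recruitment.** The inclusion criterion reads: "participants must have an ASSIST score of 11 or higher for alcohol and a score of 4 or higher for other substances". Marijuana is not excluded.

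**Analysis Plan.** Specific Objectives 1 to 3 describe one set of analyses of consumption, risk and symptoms. They name no substance and do not repeat the split by substance.

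**The concern.** Three statements in the article should agree: which substances the hypotheses cover, which are evaluated separately, and how many evaluations the sample size supports. They give four, at least three, and two.

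The gap falls on marijuana. It is a named hypothesis, yet the Sample Size section mentions it only as something that overlaps with the other substances. If the plan is followed at its stated minimum, the trial can finish without a separate marijuana result. If a marijuana evaluation is decided on later, that choice could be made after data have been seen.

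Meanwhile the plan does commit to separate evaluations of cocaine and cocaine base paste, which the article's background figures show to be the less common drugs. Those evaluations may have too few participants for the stated power.

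**Working it through.** **1. The lists side by side**

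| Substance | Hypotheses 1 and 2 | Committed separate evaluation (Sample Size) | Named in Analysis Plan |
|---|---|---|---|
| Alcohol | yes | yes | no |
| Marijuana | yes | no, overlap only | no |
| Cocaine | yes | yes | no |
| Cocaine base paste | yes | yes | no |

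**2. How common the drugs are in the article's own figures**

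- Abstract, past year: "the prevalence rates were 12.5% for marijuana, 0.8% for cocaine, and 0.4% for cocaine base paste". Marijuana is 12.5/0.8 = 15.6 times cocaine and 12.5/0.4 = 31 times paste.
- Overview, past month: 12.7%, 1% and 0.4%.
- Psychosocial Variables, arrestees, past year: 48.4%, 21% and 11.4%. Marijuana is 48.4/21 = 2.3 times cocaine and 48.4/11.4 = 4.2 times paste. Urine results in the same section are 58% marijuana and 30% cocaine.

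The order is the same in every source. The ratios vary widely, and none describes the trial's entrants.

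**3. Reproducing the sample size**

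Inputs from Sample Size and Specific Objective 3: f = 0.12, α = 0.05, power 80%, k = 2 groups, m = 4 measurements. Assumed, because the article does not give them: correlation between measurements ρ = 0.5 and sphericity ε = 1.

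- Noncentrality λ = f²·N·m/(1 − ρ) = 0.0144 × 96 × 4/0.5 = 11.06
- df1 = (k − 1)(m − 1) = 3 and df2 = (N − k)(m − 1) = 94 × 3 = 282
- Power at N = 96 is 0.800, so the plan's 96 reproduces.
- 96/(1 − 0.40) = 160, and 320/160 = 2.

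**4. What 320 supports**

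Recruits needed without overlap: 3 × 160 = 480 for three substances and 4 × 160 = 640 for four.

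Power if 320 is split evenly with 40% attrition:

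| Separate substances | Recruited each | Retained each | Power each |
|---|---|---|---|
| 2 | 160 | 96 | 80% |
| 3 | 106.7 | 64 | 60% |
| 4 | 80 | 48 | 47% |

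Power for one substance by its share of the 320, on the same assumptions:

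| Share | Recruited | Retained | Power |
|---|---|---|---|
| 10% | 32 | 19.2 | 20% |
| 20% | 64 | 38.4 | 38% |
| 30% | 96 | 57.6 | 55% |
| 40% | 128 | 76.8 | 69% |
| 50% | 160 | 96 | 80% |

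**5. Overlap needed to restore 80%**

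Each substance needs 160 of the 320, which is half of all participants. Participants would have to count towards 480/320 = 1.5 substances on average for three evaluations and 640/320 = 2 for four.

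**6. Sensitivity to ρ**

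- ρ = 0.3: 134 retained, and 134/0.6 = 223.3, so 224 recruits per substance. The 320 would not cover two.
- ρ = 0.7: 60 retained, and 60/0.6 = 100 recruits per substance. Three evenly sized groups (300) would fit and four (400) would not.

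**The case against.** **The list is a minimum.** The words *at least* set a floor, and the same sentence speaks of evaluation by substance type in general. A reader might infer that marijuana is left out or will have no evaluation of its own. The text does not support that: a separate marijuana evaluation is uncommitted, not excluded. But a minimum list that omits one of four named hypotheses still does not match those hypotheses.

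**Eligibility may be narrower than it looks.** A reader might infer that marijuana-only users enter the trial and fall into none of the named evaluations. Read literally, the *and* in the inclusion criterion requires risky alcohol use as well, so no marijuana-only user qualifies and every entrant falls within the alcohol evaluation. The separate cut-offs in the ASSIST section make an *or* reading plausible, but the article does not settle it. The mismatch holds either way, because users of both alcohol and marijuana are eligible.

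**The literal reading also helps the sizing.** If every entrant counts for alcohol, 320 could cover all three named substances. That would still need 160 cocaine users and 160 paste users among the 320, which the background figures make doubtful.

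**The prevalences are weak evidence of the trial's mix.** A reader might infer that about 90% of drug entrants use marijuana (12.7/14.1 from the Overview, 12.5/13.7 = 91% from the Abstract). These are general-population rates of any use, not of ASSIST-positive patients who consent. They are also inconsistent: past-month marijuana (12.7%) exceeds past-year (12.5%), past-month cocaine (1%) exceeds past-year (0.76%), and the 0.4% for paste is past-year in the Abstract but past-month in the Overview. Only the ordering is usable, and alcohol may be larger than any drug group.

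**Detail may sit in an analysis plan.** A full list of analyses by substance can reasonably be left there. The point here is different: the article itself states two lists and a sample size that do not agree.

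**Conclusion.** The point holds as a mismatch between stated texts. The hypotheses cover four substances, separate evaluation is committed for three, and the sample size supports two at 80% power when the groups do not overlap. Marijuana is the hypothesised substance without a commitment.

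Without overlap and with an even split, power is about 60% for each of three substances and 47% for each of four. It is 20% for a substance making up a tenth of the sample. These figures rest on f = 0.12, 40% attrition, ε = 1 and ρ = 0.5, the correlation at which the plan's 96 reproduces. Substantial overlap would raise them, but the article gives neither the expected overlap nor the expected number of users of each substance.

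The calculation of 96 and 160 is not in dispute, and the trial is not invalidated. This should be corrected while recruitment is open and, as the article reports, no analyses have been done.

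**What to change.** In the Sample Size section:

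1. Add marijuana to the separately evaluated substances, so that the list matches the Hypotheses, and carry the same list into the Analysis Plan.
2. State that 320 covers two non-overlapping evaluations at 160 each, and that 80% power does not apply to each of three or four substances unless they overlap substantially. Give the expected number per substance and the overlap assumed.
3. State that any substance with far fewer completers than the assumed 96 will be reported as an estimate with a confidence interval, not as a test of effectiveness. Fix the threshold before any outcome data are examined.

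The wording of the inclusion criterion should also make clear whether both cut-offs or either one is required, because the expected overlap depends on it.

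The cost is wording in the protocol and analysis plan. Marijuana use is already covered by the hypotheses, and the change needs no additional recruitment if the claims are limited as in item 3. The downside is one more named evaluation and weaker claims for the rarer substances.

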### Analysis Plan

For quantitative-specific objective 3, we will use the standard *P*<.05 criterion to make inferences. Tests to detect any potential differences between individuals who received interventions from either social workers or psychologists will be conducted. The analysis approach for each specific objective is described in the following sections.

#### Specific Objective 1

The first specific objective aims to determine whether the SFBI reduces substance use patterns and risk-level substance use of participants at the 3-month, 6-month, and 9-month follow-ups (post baseline). A descriptive analysis of the recorded variables will be conducted for each participant in the experimental group, pretreatment, and at 3 months, 6 months, and 9 months post baseline. Minimum and maximum values will be reported, and the normality of their distribution will be assessed using frequency histograms and the Shapiro-Wilk normality test. Categorical variables will be described using absolute and percentage frequencies. For individuals participating in the experimental group, the following analyses will be conducted separately at each posttreatment measurement (3 months, 6 months, and 9 months): the change in frequency and quantity of consumption according to the TOP instrument will be calculated for each participant, with the mean change and its corresponding CI estimated, and a paired repeated-measures ANOVA conducted to evaluate whether there is a significant treatment effect on the average weekly consumption; if the normality assumption is not met, the nonparametric Wilcoxon signed-rank test will be used. In addition, the percentage of individuals who decrease their risk category will be calculated, and their respective CIs estimated, and, since the TOP contains categorical items, the McNemar test will be applied to evaluate whether significant changes occurred.

#### Specific Objective 2

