The third specific objective aims to determine whether participants receiving the SFBI improve their substance use patterns, substance use risk level, consequences of substance use, and mental health symptoms as compared with those receiving a minimal intervention. A descriptive analysis of the recorded variables will be conducted for each participant in both experimental and control groups at baseline and at 3 months, 6 months, and 9 months post baseline. Quantitative variables will be described using mean, SD, median, minimum, and maximum values, and their distribution normality will be assessed using frequency histograms and the Shapiro-Wilk normality test. Categorical variables will be described using absolute and percentage frequencies. For each posttreatment measurement (3 months, 6 months, and 9 months), the following analyses will be conducted: the change in substance use patterns and substance use risk level (TOP) will be calculated for each participant in both experimental and control groups, and the mean with its corresponding CI will be estimated; the change in the PHQ-9 score will be calculated for individuals in both experimental and control groups, and the mean with its corresponding CI will be estimated; the change in the GAD-7 score will be calculated for individuals in both experimental and control groups, and the mean with its corresponding CI will be estimated. Baseline characteristics, including demographic background and sociofamilial situation, of participants in the control and experimental groups will be compared, with *t* tests or Wilcoxon-Mann-Whitney tests used for quantitative variables when the normality assumption is unmet, and the Fisher exact test used for categorical variables. Given that this is a superiority design, 1-tailed tests will be used for the following comparisons. The mean decrease in monthly consumption will be compared between individuals in the experimental and control groups using a mixed ANOVA, with group (experimental and control) as the between-subjects factor and time of measurement (pretreatment, 3 months, 6 months, and 9 months) as the within-subjects factor. Similarly, mean PHQ-9 scores will be compared between the two groups using a mixed ANOVA, with group (experimental and control) as the between-subjects factor and time of measurement (pretreatment, 3 months, 6 months, and 9 months) as the within-subjects factor, with the Friedman-aligned ranks test applied if the variable normality assumption is unmet. Finally, the percentage of individuals who decrease their substance use patterns and risk (TOP) will be compared between the experimental and control groups, using the Fisher exact test.

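### The target of 320 is sized as twice one evaluation, but at least three substances are evaluated separately, so 80% power is not assured for each and is very unlikely for cocaine and cocaine base paste

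*Protocol article*

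**What the plan says.** The Sample Size section of the protocol article takes an effect of "Cohen *d*=0.24 for polysubstance use, equivalent to Cohen *f*=0.12", 80% power and a 5% significance level, and sizes one test: "For the interaction effect between within-subject and between-subject factors in mixed ANOVA". The result is 96 individuals, raised to 160 for 40% attrition. The section then announces separate evaluations by substance, "evaluating its effectiveness separately for at least alcohol, cocaine, and cocaine base paste, considering possible overlaps between them and marijuana", and concludes: "Thus, we plan to recruit 320 participants".

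Other sections bear on this:

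- **Hypotheses** name four substances: alcohol, marijuana, cocaine and cocaine base paste.
- **Recruitment** is through ASSIST screening at routine preventive check-ups, with no quota by substance.
- **Data Collection** stratifies randomization by center. Substance is not mentioned.
- **Analysis Plan**, for the between-group objective: "we will use the standard *P*<.05 criterion to make inferences".
- **Abstract, Background:** "In the past year, the prevalence rates were 12.5% for marijuana, 0.8% for cocaine, and 0.4% for cocaine base paste". It also reports that 21% of adults have had a severe alcohol use episode.

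**The concern.** The last step of the sample size argument does not follow from what precedes it. One evaluation needs 160 recruits. At least three separate evaluations are promised, yet the multiplier is two. Overlap between substances could close the gap, and the section mentions overlap, but it gives no figure for it and no expected count for any substance. A reader will take 320 to deliver 80% power for each named substance.

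If it does not, the cocaine and base paste results would be presented as tests of effectiveness while resting on few people. A null result there could be read as showing that the intervention does not work for those substances. Conversely, if several substances are each treated as confirmatory at .05, one chance finding among them is more likely than 5%. The trial is meant to inform public policy, so either misreading would matter.

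**Working it through.** **Inputs from the protocol.** f = 0.12, power 80%, alpha 0.05 and attrition 40% (Sample Size); k = 2 groups and m = 4 measurements (Analysis Plan, Specific Objective 3: "time of measurement (pretreatment, 3 months, 6 months, and 9 months) as the within-subjects factor").

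**Assumed, because not stated.** Correlation among repeated measures ρ = 0.5 and sphericity (ε = 1). These values reproduce the protocol's 96; ρ = 0.3 would give 134 and ρ = 0.7 would give 60.

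**Step 1: reproduce the plan's figures.** For the within-between interaction, λ = f²·N·m/(1−ρ), df1 = (k−1)(m−1), df2 = (N−k)(m−1).

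- N = 96: λ = 0.0144 × 96 × 4/0.5 = 11.06, df = 3 and 282, power 0.800. N = 94 gives 0.791, so 96 is the smallest even N.
- Attrition: 96/0.6 = 160.
- Target: 2 × 160 = 320.

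**Step 2: what separate evaluations need.** Without overlap, three substances need 3 × 160 = 480 recruits and four need 640. For 320 to be enough, participants must average 480/320 = 1.5 (three) or 640/320 = 2.0 (four) qualifying substances each, and every substance must itself reach 160.

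**Step 3: power by number of users, overlap allowed.** One participant may count for several substances. Completers = 0.6 × recruits.

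| Recruited users of the substance | Share of 320 | Completers | Power |
|---|---|---|---|
| 320 | 100% | 192 | 98% |
| 240 | 75% | 144 | 94% |
| 160 | 50% | 96 | 80% |
| 107 (equal split over three) | 33% | 64 | 60% |
| 80 (equal split over four) | 25% | 48 | 47% |
| 32 | 10% | 19 | 20% |

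So 80% power for a substance requires that half of all recruits use it.

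**Step 4: is half plausible for the rarer substances?** On the quoted figures, cocaine and base paste are between 12.5/0.8 ≈ 16 and 21/0.4 ≈ 53 times rarer than marijuana use or a severe alcohol episode. Two illustrations follow, both assuming one substance per recruit.

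- *Mix in proportion to the quoted figures.* The weights 21, 12.5, 0.8 and 0.4 sum to 34.7. Of 320 recruits, about 194 fall to alcohol, 115 to marijuana, 7 to cocaine and 4 to base paste. Alcohol then has 116 completers and 88% power; cocaine and base paste are below 10%.
- *Cocaine and base paste over-represented tenfold.* The weights 21, 12.5, 8 and 4 sum to 45.5. The counts are about 148, 88, 56 and 28. Cocaine has 34 completers and 34% power; base paste has 17 completers and 18% power.

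**Step 5: error rate.** Each test at .05 has a 5% error rate for its own substance. Across independent tests the familywise rate is 1 − 0.95³ = 14.3% for three and 1 − 0.95⁴ = 18.5% for four.

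**The case against.** Four objections carry weight.

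1. **Overlap is acknowledged.** The section expects the same people to contribute to several substances. Read literally, the inclusion criterion in Recruitment requires a qualifying alcohol score *and* a qualifying score for other substances, so every participant would have at least two. This stands, and it is why 480 or 640 cannot be called the required size. But overlap helps a given substance only if half the sample uses that substance. The second substance could be marijuana throughout, which would do nothing for cocaine or base paste.

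2. **The prevalence mix is not a forecast.** It combines a severe alcohol episode with past-year drug use, in the general population, whereas eligibility rests on ASSIST risk scores in primary care. The tenfold factor has no source in the protocol. This stands too: the counts of 56 and 28 are illustrations. The conclusion rests on the 50% threshold, not on them.

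3. **Some substances may be well powered.** A reader might infer that 80% power fails for every substance. The figures do not support that: alcohol has 88% with 194 recruits and no overlap at all.

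4. **Error control may be specified elsewhere.** A reader might also infer that the 5% error rate fails per substance. It does not; only the familywise rate rises, and positive correlation between overlapping tests would usually lower it below the independence figures. The article states no rule that one significant substance counts as success, and a multiplicity rule could sit in an analysis plan that is not shown. The error-rate issue is therefore secondary and conditional.

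**Conclusion.** The concern holds as a fault in a stated sample size argument. The protocol's 96 and 160 reproduce for one evaluation; the step to 320 is not justified for at least three. Power of 80% is assured only for a substance used by at least 160 of the 320 recruits. Alcohol may well meet that. Nothing in the plan secures it for cocaine or base paste, and the protocol's own prevalences and recruitment route make it very unlikely.

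The size depends on the unknown mix: about 60% power each for three equal non-overlapping groups, about 47% for four, and about 34% and 18% for 56 cocaine and 28 base paste recruits. All of these assume f = 0.12, ρ = 0.5, sphericity and 40% attrition. If several substances are confirmatory without adjustment, the familywise error under independence is about 14% (three) or 19% (four), while each single test stays at 5%.

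**What to change.** Revise the Sample Size section to:

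- state, for each substance, the expected number of users among the 320, the expected overlap, and the power that results;
- claim 80% power only for substances expected to reach 160 recruits;
- present cocaine, base paste and any other low-count substance as descriptive estimates with confidence intervals, not as tests of effectiveness.

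If more than one substance stays confirmatory, state in the Analysis Plan that Holm or a fixed testing order will be used.

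The cost is wording; no extra participants are needed. The protocol reports that recruitment runs to December 2026 and that no analyses have been done, so the change can still be made before results are seen. The price is giving up confirmatory claims for the rare substances, which the trial is very unlikely to be able to support.
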